**Methods and analysis::**

This is a pilot randomized controlled trial with the objective of investigating the effect of Jia Wei Liang Xue Xiao Feng San granules on relapse rate of recurrent PV and the correlation between Psoriasis area severity index (PASI) and key psoriasis-related cytokine changes and the number of cells. A total of 102 participants were recruited for this study, including 72 patients with recurrent PV, 15 healthy volunteers and 15 patients with psoriasis vulgaris who have recovered for more than 1 year. A total of 72 patients, with recurrent PV, will be randomized (1:1) to receive the oral Chinese herbal medicine Jia Wei Liang Xue Xiao Feng San or the oral Acitretin Capsule treatments for a period of 8 weeks. After this period, participants whose PASI scores improvement reached more than 75%, will undergo a 52-week follow-up phase.

The primary outcome measures are as follows:

The secondary study outcomes will include:

This trial may provide a novel regimen for recurrent PV patients if the granules decrease recurrence rate without further adverse effects.

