#### Primary outcomes

3.5.1

(1)PASI: assess the severity of the disease.(2)Laboratory assessments: the number and distribution of Th1, Th2, Th17, Treg, Th22, and Th9 cells will be determined by ELISA. The expression of the transcription factors T-bet, GATA3, ROR gamma t, Foxp3 gene will be investigated by PCR and WB. The screening of cytokines, such as IFN-gamma, IL-4, IL-17A, IL-17F, IL-22, TGF-beta, IL-10 and IL-9 will be performed by Bio-Plex suspension chip.(3)Recurrence rate = recurrence cases/follow-up cases ∗100%

Note:

No recurrence criteria: the same as the end of treatment and lesion limitation. Recurrence criteria: new skin lesions appearing in the patients who were clinically cured or have the original skin lesions expanding, the color turning red, the scale increasing and the PASI score increasing for ≥ 1.

(1) Mitigation period: this remission period - the last remission period.

Note:

The last remission period: the time from the last clinical cure to the recurrence. This remission: the time interval from the end of JWLXXF treatment to the next recurrence.

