### Sample size calculation

3.8

Due to the unknown potential primary outcome at this stage, the sample size was calculated by reference to a standardized effect size. An effect size of 0.9 SD was chosen with consideration of the drug cost and patients’ motivation to adhere to the treatment. To detect a difference of 0.9 SD with 90% power using a 5% significance level, a sample size of 30 per arm would be required. Considering 20% dropout rate, the total sample size should be adjusted to 36 for each group.

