### Statistical analysis

3.10

SPSS Statistics 17.0 (IBM SPSS Inc., Armonk, NY) will be used for the statistical analysis of data, which will be carried out by independent statisticians. The Chi-square test will be used to evaluate the basic baseline characteristics and primary outcomes of the 2 groups. The Spearman rank correlation analysis of the correlation between PASI and biochemical indexes, will be used. The secondary outcomes will be evaluated by means, standard deviations and medians. The one way ANOVA test will be used to compare the mean of multiple samples, the LSD test for the homogeneous variance, and the Tamhane T2 test for the uneven variance. *P* < .05 will be considered as statistically significant.

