### Test technology design basis

4.3

From the cellular, molecular, proteic and genomic perspectives, the mechanism of the JWLXXF compound in the treatment of psoriasis and its role in recurrence prevention was discussed. The target of the drug was comprehensively analyzed, so that the experiments could complement and confirm each other. ELISA, WB and PCR technologies are the basic means of scientific research and application in dermatology. The method of liquid-phase protein chip organically integrates microsphere, laser detection technology, fluid dynamics, high-speed digital signal processing system and computer operation function. Not only the detection speed is very fast, but it also provides specificity and sensitivity in immunodiagnosis and protein molecular interaction analysis that are often beyond the conventional technology.

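### Section 3.5.1 assigns a primary outcome of T-cell subset numbers to ELISA, which gives a concentration and cannot count cells; no cell-counting method is named anywhere

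*Protocol article*

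**What the plan says.** The abstract (Methods and analysis) gives the objective as the effect on relapse rate together with "the correlation between Psoriasis area severity index (PASI) and key psoriasis-related cytokine changes and the number of cells". Cell numbers are therefore one side of a correlation that the trial sets out to estimate.

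Section 3.5.1 (Primary outcomes), item 2, lists three kinds of laboratory measurement and gives each its own method:

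- T-cell subsets: "the number and distribution of Th1, Th2, Th17, Treg, Th22, and Th9 cells will be determined by ELISA".
- Transcription factors: "The expression of the transcription factors T-bet, GATA3, ROR gamma t, Foxp3 gene will be investigated by PCR and WB".
- Cytokines, a list of eight that ends: "IL-10 and IL-9 will be performed by Bio-Plex suspension chip".

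Section 3.10 (Statistical analysis) plans the correlation: "The Spearman rank correlation analysis of the correlation between PASI and biochemical indexes, will be used".

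Section 4.3 (Test technology design basis) says that "ELISA, WB and PCR technologies are the basic means of scientific research and application in dermatology", and then describes the liquid-phase protein chip. It names no other technology.

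**The concern.** The quantity named and the instrument named for it do not match. A subset number or distribution is a count, or a share, of cells that carry a defining marker. An ELISA reading is an amount of analyte per unit of sample. One cannot be read off the other, because the second contains no information on how many cells there were or of which kind.

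If the text is followed literally, there are two possible results. Either the outcome is never produced, or concentrations are tabulated under a cell-number label. In the second case the Spearman analysis would correlate PASI with a protein level while the report spoke of T-cell subsets. A statement on which subsets change with treatment, or move with PASI, would then have no measurement behind it.

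**Working it through.** The plan gives no figure to reproduce here, and the sample-size inputs in section 3.8 do not enter. The check is whether any named method can deliver the named quantity.

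**Step 1: match each quantity to its method (section 3.5.1, item 2).**

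| Quantity | How many named | Method stated | What the method returns | Match? |
|---|---|---|---|---|
| T-cell subset number and distribution | 6 | ELISA | analyte concentration | no |
| Transcription-factor expression | 4 | PCR and Western blot | gene or protein expression | yes |
| Cytokines | 8 | Bio-Plex suspension chip | cytokine concentration | yes |

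**Step 2: look for another method that could fill the first row.** PCR and Western blot are assigned to transcription factors and the chip to cytokines. The transcription factors may give indirect evidence on cell lineage, but they do not give counts. Section 4.3 adds no cell-counting technology, and neither does any other section. Flow cytometry and ELISpot are not mentioned.

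**Step 3: trace where the quantity is used.** It appears in the objective (abstract) and as a primary outcome (3.5.1). The correlation in 3.10 is with biochemical indexes, so it can still be run on the cytokines and transcription factors. Only its cell-number part is lost.

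**Step 4: size.**

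- Laboratory quantities named: 6 + 4 + 8 = 18. Affected: 6/18, or one third. The cytokine list is introduced as examples, so 18 is the minimum total.
- Participants: the article does not say who provides samples for these assays. Section 2 schedules laboratory efficacy assessments at the end of week 8 in text about the 72 randomized patients. If the two comparison groups are sampled as well, the number is 72 + 15 + 15 = 102. The range is 72 to 102, and both ends are assumptions.
- Patients already in the trial: section 4.4 reports 60 recruited. If all 60 belong to the randomized group, that is 60/72 = 83%. If the count includes all 15 recovered patients, it is 45/72 = 63%. In either case most randomized patients had entered before any change of assay could take effect.

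**The case against.** **The article condenses a fuller protocol.** That excuses silence. Had 3.5.1 named no assay, there would be no point to raise. It does name one, and the one it names does not fit.

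**It may be a drafting or translation slip.** This is possible. ELISA is tied to cell numbers in one sentence only. Section 4.3 lists the technologies in general terms and does not assign ELISA to counting cells, so it is weak corroboration. One therefore cannot predict that the laboratory will report concentrations as counts. But if a cell-counting method is in use, the published definition of a primary outcome is wrong and still needs correcting.

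**Only part of one item is affected, in a pilot trial.** This stands. The clinical outcomes and the other laboratory measures can be produced as written, and the comparison of the two treatments does not depend on the subset numbers. The text does, however, list them as primary and put them in the objective, so they cannot be dismissed as incidental.

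**Readings that go too far.** A reader might infer that the outcome is lost for all 102 participants, but the article does not say who is sampled, and Table 1 is not shown. A reader might infer that any subset conclusion would be false; the text supports only that it would be unsupported. A reader might also infer that the ELISA merely repeats the Bio-Plex panel. The ELISA analytes are not named, so this cannot be checked. Lastly, one might suppose that flow cytometry could be run on the samples already taken. No specimen type is stated for these assays, and nothing shows that viable cells were kept.

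**Conclusion.** The point holds for the cell-number outcome and its correlation with PASI: with the assay stated, neither can be produced. Six named primary laboratory quantities, one third of those listed, are affected. ELISA readings presented as subset numbers would give no support to any statement about subsets. The rest of the primary and secondary outcomes stand as far as this point is concerned.

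The conclusion rests on the general fact that a standard ELISA measures concentration and does not enumerate cells, and on the absence of any cell-counting method from the article. The number of participants (72 to 102) and the specimen are assumptions. What the laboratory actually does is not known from the article. The text needs correction whichever method is in use.

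**What to change.** **Default: align the outcome with the assay.** In 3.5.1, redefine the ELISA outcome as the concentration of named analytes in a named specimen, and take the number and distribution of the six subsets out of the outcomes. In the abstract, shorten the objective that now reads "key psoriasis-related cytokine changes and the number of cells" so that it no longer refers to cells. Draw no conclusion on cell numbers in the report. This costs wording only and can be done for all patients, including those already recruited.

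**Alternative: align the assay with the outcome.** If the laboratory in fact uses, or can use, a cell-enumerating method such as flow cytometry, name it in 3.5.1 and 4.3, and report each subset both as a percentage of CD4+ cells and as an absolute count. This requires fresh or viably frozen cells, including from the 60 patients already recruited. The cost is the new assay, its reagents and suitable cell handling. If such cells were not kept, their counts cannot be recovered and the default applies.

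The investigators should confirm with the laboratory which method is in use before choosing, and state which participants are sampled and when.

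### At least 21 primary measures share one 5% threshold, with no main outcome, order or adjustment, in a trial sized for a single 5% test

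*Protocol article*

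**What the plan says.** **Primary outcomes (section 3.5.1).** Six groups of measures stand under this heading:

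- Clinical severity, by the PASI score (one measure).
- T-cell subsets, six of them, in these words: "the number and distribution of Th1, Th2, Th17, Treg, Th22, and Th9 cells will be determined by ELISA".
- Four transcription factors, each measured by two methods (PCR and WB).
- Cytokines on a Bio-Plex chip. Eight are named, but only as examples, so the list is open-ended.
- Relapse during follow-up, defined by the formula "Recurrence rate = recurrence cases/follow-up cases".
- Length of remission, which is placed after a note and with restarted numbering but still under this heading: "Mitigation period: this remission period - the last remission period".

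**Statistical analysis (section 3.10).** Chi-square is assigned to the primary outcomes of the two arms, and Spearman correlation to PASI against the biochemical indexes. One-way ANOVA is assigned to means of several samples, followed by "the LSD test for the homogeneous variance, and the Tamhane T2 test for the uneven variance". One threshold, P < .05, closes the section. No primary outcome is ranked above another, and no adjustment for several tests is mentioned.

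**Sample size (section 3.8).** The calculation opens with "Due to the unknown potential primary outcome at this stage". It then uses a difference of 0.9 SD, 90% power and a 5% level to reach 30 per arm, raised to 36 per arm for 20% dropout.

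**The concern.** The sample size rests on one comparison at 5%, but the list of primary outcomes allows at least 21. Nothing in the article says which one decides whether the trial succeeded. Eighteen of the 21 are laboratory markers. Under the plan as written, a single marker with P < .05 could be reported as a positive primary outcome, even if the relapse result, which leads the stated objective, showed nothing.

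The post-hoc rule adds a smaller problem. LSD makes no allowance for the number of group pairs, whereas Tamhane T2 does. Protection across pairs therefore depends on which way the variance check falls. Neither procedure allows for the number of outcomes.

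**Working it through.** **1. The plan's own figure.** For 0.9 SD, two-sided 5% (sidedness is not stated) and 90% power, the normal approximation gives n = 2 × (1.960 + 1.282)² / 0.9² = 2 × 10.51 / 0.81 = 25.9, so 26 per arm. The exact t-test gives 27. The stated 30 is not reproduced, but it errs on the safe side: t-test power at 30 per arm is 92.9%. For dropout, 30 × 1.2 = 36, against 30 / 0.8 = 37.5, so 38. Neither difference matters here. What matters is that the calculation covers one test at 5%.

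**2. Count of primary measures (section 3.5.1).** PASI 1 + T-cell subsets 6 + transcription factors 4 + named cytokines 8 + recurrence rate 1 + remission period 1 = 21. Counting PCR and WB separately gives 25. Also splitting number from distribution of cells gives 31. Leaving out the remission period, whose numbering restarts under the same heading, gives 20.

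**3. Error rate if each is tested at 5% between arms, all nulls true.**

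The expected number of false positives is 21 × 0.05 = 1.05, whatever the correlation.

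Under independence the chance of at least one is 1 − 0.95^k:

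| k | Chance of at least one false positive |
|---|---|
| 20 | 64.2% |
| 21 | 65.9% |
| 25 | 72.3% |
| 31 | 79.6% |

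The article gives no correlations, so a common correlation ρ is assumed. With c = 1.96 and Z standard normal, the chance is 1 − E[{Φ((c − √ρ Z)/√(1−ρ)) − Φ((−c − √ρ Z)/√(1−ρ))}^21], evaluated numerically:

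| ρ | All 21 correlated | 18 laboratory markers correlated, 3 clinical outcomes independent |
|---|---|---|
| 0 | 65.9% | 65.9% |
| 0.2 | 60.6% | 61.9% |
| 0.3 | 55.5% | 57.9% |
| 0.4 | 49.5% | 53.3% |
| 0.5 | 42.9% | 48.3% |
| 0.8 | 22.8% | 32.8% |

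The 50% line is crossed at ρ of about 0.39 in the first case and 0.47 in the second.

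**4. LSD.** Assume the ANOVA covers the two arms (36 each), the healthy volunteers (15) and the recovered patients (15). That gives 4 × 3 / 2 = 6 pairs. Simulation with 40,000 replicates and equal variances gives the chance of at least one false pairwise difference per outcome:

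- No group differs, LSD only after a significant ANOVA: 4.8%.
- One group of 15 shifted by 3 SD, the other three equal: 12.0%.
- Two groups shifted together: 9.3%.
- No group differs, LSD without the ANOVA gate: 19.4%.

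A large shift in one group makes the ANOVA significant almost every time, so the three pairs among the equal groups are then each tested at an unadjusted 5%.

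**5. What two remedies do.** One designated primary keeps the error rate at 5% and leaves the single-test basis of section 3.8 intact. Bonferroni over 21 sets each level at 0.05 / 21 = 0.00238. Power for 0.9 SD at 30 evaluable per arm then falls from 92.9% to 62%, and 90% power needs 49 evaluable per arm, or 49 / 0.8 = 61.25, so 62 with dropout.

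**The case against.** **The laboratory markers may have only a correlational role.** The abstract speaks of correlating PASI with cytokine changes and cell numbers, and section 3.10 gives Spearman for that. No sentence says that 18 markers each receive a between-arm efficacy test. This has weight, and it is why the figures above are conditional. But section 3.5.1 does list the markers as primary, and section 3.10 sends the primary outcomes of the two arms to testing. Even if only PASI, recurrence and remission period were compared between arms, the error rate under independence would be 1 − 0.95³ = 14.3%.

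**A reader might infer that a false-positive primary result is more likely than not.** The article does not support this as a general statement. It holds only if the common correlation is below about 0.4, and immune markers of this kind may well be more strongly correlated.

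**A reader might take section 3.8 as admitting that no primary outcome exists.** The phrase introduces a standardised effect size, so it may mean only that the expected size of the effect was unknown. The point does not depend on it. The single 5% test in the calculation is enough.

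**LSD is not fixed for every multi-group comparison.** It applies only where variances are homogeneous, and the article does not say that the ANOVA covers all four groups. The 12% also includes pairs with the non-randomised groups, so it is not the error rate of the randomised comparison. This stands, and LSD is a side issue.

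**It is a pilot with a relapse objective, and an analysis plan may set an order.** The objective and the abstract's closing condition do point to relapse, which makes displacement by a chance marker less likely. They do not rank the outcomes. The finding rests on what the article fixes (the primary list and the threshold), which a later plan would have to override.

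**Conclusion.** The point holds. The article fixes at least 21 primary measures and one 5% threshold, with no main outcome, order or adjustment, against a sample size for one test. If all are tested between arms and all nulls are true, the chance of at least one false-positive primary result ranges from 66% under independence to 23% at a common correlation of 0.8, well above 5% throughout. The range rests on assumed equal correlations and two-sided tests.

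The LSD figure of about 12% is secondary. It assumes four groups, equal variances and one group that truly differs.

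Two further inferences are not part of this finding. One is that ELISA cannot deliver the cell numbers: this is a laboratory question that the article does not settle. The other is that the recurrence denominator should become all randomised patients: this would change the estimand and needs its own argument.

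**What to change.** Before any outcome data are analysed, and in a dated amendment:

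1. Name one primary outcome that matches the relapse objective, namely recurrence, with week-8 PASI as key secondary.
2. Label the cell, expression and cytokine measures, and their correlations with PASI, exploratory, with false-discovery-rate control.
3. Replace LSD by Tukey-Kramer where variances are homogeneous, and keep Tamhane T2 where they are not.
4. Restate the power in section 3.8 for the outcome chosen.

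**Cost.** No further patients are needed to control the error rate, unlike Bonferroni over 21. The laboratory results lose primary status. The change comes during the trial, since the Trial status section reports 60 patients already recruited, so its date and its independence from outcome data must be documented.

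The stated 90% power for 0.9 SD refers to a continuous outcome and does not carry over to recurrence. On the arcsine scale an effect of 0.9 corresponds, for example, to 50% against about 89%. Recurrence is also counted only among the responders who enter follow-up, so the evaluable number may fall below 30 per arm. Power for recurrence could therefore be well below the stated figure, and the article should say what it is.

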**Table 1 T1:**
[figure not shown]
Evaluation measures and time points.

The 72 patients with recurrent PV, whose PASI scores improvement are more than 75%, will undergo a 52-week follow-up phase (week 9 to week 60), with further data collection, including assessment of PASI, routine chemical examinations, recurrence rate, remission period (This remission period - the last remission period) (Table 1).

For the 52-week follow-up phase, participants will continue to record symptoms in their daily or weekly diaries. At week 60, participants will attend an end of follow-up assessment (9th visit) which will mark the end of the trial.

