### Clinical efficacy evaluation basis

4.2

For moderate and severe psoriasis, PASI score is still the “gold standard” to evaluate the severity of psoriasis.^[29]^ According to the research, patients with sustained and efficient response to PASI score have a better quality of life score.^[30]^ According to the requirements of the new drug effective standard, after three months of test, the effective standard is a 75% improvement of the PASI score, which is called PASI75.^[29]^ PASI75 combined, with the pruritus score and DQOLS, can evaluate the short-term efficacy of JWLXXF. It needs a certain time to follow up on the recurrence rate and remission period to determine the long-term effect. After 8 weeks of treatment, patients with a pai75 will be followed up and this period will start from the end of the treatment. If there is no recurrence, the follow-up period is 1 year. If there is recurrence, the recurrence of the disease is the end point of the follow-up.

According to the guiding principles for clinical research on new drugs of traditional Chinese medicine (Part III), issued by the Ministry of health in 1997 and the directions of new drugs clinical research (try out) issued by the State Food and Drug Administration in 2002, the recurrence criteria are: new skin lesions appear in the patients who are cured clinically, or the original skin lesions expand, turn red, scale increase, and PASI score increase for ≥1. No recurrence criteria: the same as that at the end of treatment, but with limited skin lesions.^[31]^

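### The primary recurrence rate ignores time under observation and leaves its denominator undefined, so any loss before 52 weeks makes it too low or too high, depending on the reading

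*Protocol article*

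**What the plan says.** Section 3.5.1 (Primary outcomes) gives the measure as "Recurrence rate = recurrence cases/follow-up cases ∗100". It has no time element, and the section does not say whether *follow-up cases* means everyone who enters follow-up or only those whose outcome is known.

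Section 3.10 (Statistical analysis) names the test: "The Chi-square test will be used to evaluate the basic baseline characteristics and primary outcomes of the 2 groups". No method that handles incomplete follow-up is named.

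Section 4.2 (Clinical efficacy evaluation basis) describes two ways in which follow-up ends: "If there is no recurrence, the follow-up period is 1 year" and "If there is recurrence, the recurrence of the disease is the end point of the follow-up". A patient who leaves recurrence-free in between fits neither.

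Entry is restricted. In section 2 (Methods/design, text after Table 1), patients "whose PASI scores improvement are more than 75%, will undergo a 52-week follow-up phase". The number expected to enter is not given.

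The only attrition figure is in section 3.8 (Sample size calculation): "Considering 20% dropout rate, the total sample size should be adjusted to 36 for each group". It applies to randomised patients. Section 3.1.3 (Elimination criteria) removes patients whose records are incomplete, without saying whether this reaches into the follow-up phase or the denominator of the recurrence rate.

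**The concern.** A recurrence can be recorded only while a patient is still being followed. A simple ratio compared by chi-square therefore estimates the 52-week risk only if everyone is followed to recurrence or to week 52.

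- If all entrants form the denominator, a patient lost recurrence-free at, say, week 15 counts as a full recurrence-free year, and the rate is too low.
- If only patients with a known end state are counted, someone who relapses early stays in, while someone lost recurrence-free is removed, and the rate is too high.

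The effect on relapse rate is the trial's stated objective. Because the denominator is not fixed, the direction of the error depends on a choice that could be made after the data are seen. If loss differs between arms, that choice can also decide which arm looks better.

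**Working it through.** **What the article supplies.** The 20% is a recruitment allowance: 30 × 1.20 = 36 per arm. There is no stated recurrence rate or follow-up loss to reproduce, so everything below is illustrative.

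**Assumptions (not in the article).** True 52-week recurrence p = 40%, 50% or 60%; constant recurrence and loss hazards (except in pattern C); loss unrelated to recurrence. The 20% is borrowed only as a convenient loss level.

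**Formulas (time unit 52 weeks).** Recurrence hazard λ = −ln(1 − p); loss hazard c.

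- Recurrences seen, as a fraction of entrants: R = λ/(λ + c) × (1 − e^−(λ+c))
- Lost recurrence-free: L = c/(λ + c) × (1 − e^−(λ+c))
- Recurrence-free completers: C = e^−(λ+c)
- Reading 1 (all entrants): R. Reading 2 (recurrences plus completers): R/(R + C).

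**Worked case.** With p = 0.50, λ = 0.6931. Let c = −ln(0.80) = 0.2231, so that loss acting alone would reach 20% by week 52. Then λ + c = 0.9163 and C = 0.40. R = 0.6931/0.9163 × 0.60 = 0.454, which is 9.2% too low. Reading 2 gives 0.454/0.854 = 0.532, which is 6.3% too high.

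**Three loss patterns.**

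- A: c = 0.2231, as above.
- B: c solved so that L = 0.20, meaning 20% actually leave recurrence-free (c = 0.291, 0.318, 0.353 for the three values of p). Reading 2 is then R/0.80.
- C: 20% have loss times spread evenly over weeks 0–13. R = 0.8p + 0.2 × the average of (1 − e^−λu) over u from 0 to 0.25.

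| True p | A, reading 1 | A, reading 2 | B, reading 1 | B, reading 2 | C, reading 1 |
|---|---|---|---|---|---|
| 40% | 36.2% (−9.5%) | 43.0% (+7.5%) | 35.1% (−12.2%) | 43.9% (+9.8%) | 33.2% (−16.9%) |
| 50% | 45.4% (−9.2%) | 53.2% (+6.3%) | 43.6% (−12.8%) | 54.5% (+9.0%) | 41.6% (−16.7%) |
| 60% | 54.7% (−8.9%) | 63.1% (+5.1%) | 51.9% (−13.5%) | 64.9% (+8.1%) | 50.1% (−16.5%) |

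Brackets show relative bias. At p = 50% under patterns A and B, reading 1 is 4.6 to 6.4 percentage points low.

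**Range over other recurrence risks.** For p from 10% to 90%, reading 1 is 10.2% to 6.8% too low under A and 10.7% to 17.1% too low under B. Reading 2 is 10.9% to 1.4% too high under A. If all the loss came at the very start, reading 1 would be 20% too low. If it all came at the very end, the bias would be near zero.

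**Comparison with equal loss (pattern A, 20% in both arms).** A true 30% v 50% becomes 27.1% v 45.4% under reading 1. The difference is 18.3 points instead of 20, and the ratio is 0.596 instead of 0.600.

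**Comparison with unequal loss (10% v 30%, identical true 50%).**

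- 10% loss: c = 0.1054, R = 0.6931/0.7985 × 0.55 = 0.477, C = 0.45, reading 2 = 0.477/0.927 = 0.515.
- 30% loss: c = 0.3567, R = 0.6931/1.0498 × 0.65 = 0.429, C = 0.35, reading 2 = 0.429/0.779 = 0.551.
- Reading 1: 47.7% v 42.9%, a false 4.8 points in favour of the arm that loses more.
- Reading 2: 51.5% v 55.1%, a false 3.6 points in the opposite direction.

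**The case against.** The strongest reply is that this is detail for a full protocol or SAP, and that a fixed-horizon proportion with chi-square is a legitimate pilot endpoint. Definitions of analysis sets and censoring rules can indeed sit elsewhere. But the article itself fixes the estimator in 3.5.1 and the test in 3.10, and both disregard observation time. That is a stated rule, not a gap. Section 3.5.1 also lists a remission-period outcome, which uses time to recurrence, but this does not change how the recurrence rate is calculated or tested.

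The reply is right that the comparison is robust to equal, non-informative loss. Harm to the contrast needs loss that differs by arm or is related to outcome. The regimens differ openly (section 3.2: granules three times a day against acitretin once a day, with no placebo described). However, both stop at week 8, before follow-up begins, and assessors are to be blinded, so unequal loss is possible but not shown. Even 4.8 points is small beside sampling error: with all 36 per arm in follow-up and a 50% risk, the standard error of the difference is √(2 × 0.25/36) = 11.8 points, and only responders enter.

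Two stronger readings are tempting. A reader might infer that the plan itself expects 20% loss during follow-up. It does not: the 20% enlarges the randomised sample, and no loss rate is given for the 52-week phase. A reader might also infer that lost patients are definitely scored as recurrence-free for a year, so that the bias is downward. The text does not settle this. The two end states in 4.2 and the elimination rule in 3.1.3 could equally support excluding them, which reverses the sign.

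**Conclusion.** The point holds as a defect of definition and method. The recurrence rate ignores observation time and has an undefined denominator, and with any recurrence-free loss before 52 weeks neither reading gives the 52-week risk.

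The size cannot be derived from the article. Under the stated assumptions (20% non-informative loss, true recurrence 40–60%), the all-entrants rate is about 9–14% too low in relative terms with constant hazards, and about 17% too low with loss confined to the first 13 weeks. The known-outcome rate is about 5–7% too high under pattern A and 8–10% too high under pattern B.

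The bias falls mainly on each arm's rate. The between-arm ratio is nearly unaffected by equal loss. It becomes unreliable, in a direction set by the undefined denominator, when loss is unequal. This should be corrected, but it does not by itself show that the trial's comparison will be wrong.

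**What to change.** In sections 3.5.1 and 3.10:

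- Make the primary recurrence measure the Kaplan-Meier cumulative recurrence at 52 weeks from the end of treatment, among patients who enter follow-up.
- Censor recurrence-free patients at their last attended assessment, and say so.
- Report the between-arm difference at 52 weeks with its 95% CI, and compare arms by log-rank instead of chi-square for this outcome.
- Keep the crude ratio as description only, with its denominator defined and the number lost shown per arm.

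The cost is small. Time to recurrence is already needed for the remission period in 3.5.1, and 4.2 already ends follow-up at recurrence. The date of the last attended assessment must also be used, since the remission-period definition does not call for it. Section 4.4 reports 60 patients already recruited, so the change should be recorded as a dated amendment made before recurrence data are examined by arm.

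The method still assumes that loss is non-informative within each arm. It also remains conditional on response at week 8, as the crude ratio is.
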